##### Dose Cohorts

The first phase 1 cohort (6 patients) will be randomised to starting dose of 600mg BID dose or standard of care (2:1 ratio), with subsequent planned dose escalation to 1200mg BID, to a maximum dose of 2400mg BID and a possible de-escalation dose of 300mg BID if necessary. Escalation will occur only in the case of acceptable safety and tolerability at the next lowest dose (modelled as per the Master Protocol and additional requirements for this CST). De-escalation will be guided by DLTs and SRC decisions.

For each dose level, the first two eligible participants enrolled will be randomized 1:1 to Favipiravir or standard of care. These sentinel participants will be dosed and monitored for 24 hours post-dose. If there has been no serious adverse event considered by the Investigator to be at least possibly related to the study drug and no other significant safety concern, the remainder of the cohort will be dosed. This will be documented and reviewed by the local site PI(s) with oversight from the CI.

##### Decision Making

Dose escalation will be based on review of safety data up to Day 8 on the safety population. Doses are deemed to be safe if the risk of dose-limiting toxicity (DLT) being at least 30% larger in IV Favipiravir than standard of care is less than 25%. Dose de-escalation for the starting dose will be reviewed by the SRC and guided by their decision depending on DLTs.

A two parameter Bayesian dose escalation model will be used to recommend the next cohort dose or the recommended phase II dose. The model will target a safe dose with an additional DLT risk of 20% (the target interval of 15-25%) above standard of care.

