| Sample size:                            | 
Phase I:
 
The plan is to test up to 5 dose levels of IV Favipiravir in up to 5 cohorts of 6 patients each (30 patients in total). Fewer than 5 cohorts and up to 42 patients (allowing for another two cohorts of 6 participants) may be enrolled, with the final number dependent on dose escalation decisions. Each cohort includes 4 IV Favipiravir patients and 2 SoC.
 
Phase II:
 
A maximum of 198 participants, randomised in a 1:1 ratio IV Favipiravir and placebo, will be enrolled in the phase II stage. There will be a blinded efficacy and futility review after the first 66 patients (one third of the way through the trial without pausing the recruitment).
                                                                                                                                                                                   |
| Investigational Medicinal Product/s:    | 
Favipiravir: 6-fluoro-3-hydroxypyrazine-2-carboxamide, T-705
 
Phase I: IV Favipiravir or SoC (open label)
 
Phase II: IV Favipiravir or placebo (double blinded)
 
Favipiravir is a novel nucleic acid (pyrazine molecule) analogue that interferes with viral ribonucleic acid (RNA) replication and has demonstrated activity against SARS-CoV-2 both in-vitro and in animal infection models (Wang, 2020) (Suzanne, 2020).
                                                                                                                                                                                                                                                                                                                                                                                                                                                    |

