| Primary                                                                                                                                                                                                                                             |                                                                                                                                                                                                                                                                                                                                                                                                                                                                                                                                                                                                                                                                                                                                                                                                                                                                                              |
| Safety objective: To determine the safety and tolerability of multiple doses of IV Favipiravir in patients with COVID-19

Efficacy objective: To determine the maximum safe dose of IV Favipiravir for efficacy evaluation in phase II | 

• Adverse events and serious adverse events

• Dose limiting toxicities (Safety and Tolerability of IV Favipiravir– CTCAE v5 Grade ≥3 adverse events possibly or probably related to the IMP) up to day 8

                                                                                                                                                                                                                                                                                                                                                                                                                                                                                                                                                                                                                             |

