### 4.2 TRIAL PHASES

#### 4.2.1 Dose finding (phase I)

Phase I will be open-label assessing escalating doses of IV Favipiravir compared with Standard of Care (SoC). Patients in phase I will be recruited in cohorts of 6 (randomised to IV Favipiravir: SoC in 2:1 allocation ratio), with review of safety and tolerability between cohorts.

Dose-finding will be carried out as per the Master Protocol (Master Protocol section 4.2.1).

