### 8.2.2 Treatment

#### Phase I

Participants will be randomised to receive IV Favipiravir or SoC only (2:1) on Day 1. Refer to section 6 of the CST6 protocol for further information.

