#### 9.1.1 Dose Limiting Toxicity (DLT)

Dose limiting toxicities will be defined as CTCAE v5 Grade  $\geq 3$  adverse events, independently assessed to be possibly or probably related to the IMP as per SRC charter. The assessment of relatedness is included in the DLT definition for this CST due to the potential for a high frequency of CTCAE v5 Grade  $\geq 3$  adverse events related to disease or co-morbidity in these cohort of hospitalised patients and the desire to avoid labelling potential treatments as unsafe due to misclassifying non-treatment related toxicities.

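### Phase I sets its DLT limit and dose target as risk above standard of care, but a DLT must be IMP-related, so on this text the standard-of-care risk is structurally zero

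*Protocol*

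**What the plan says.** Protocol section 10.3.1 (Phase I, Decision Making) gives two statements about dose. The safety limit is that the "risk of dose-limiting toxicity (DLT) being at least 30% larger in IV Favipiravir than standard of care is less than 25" per cent. The dose target is: "The model will target a safe dose with an additional DLT risk of 20% (the target interval of 15-25%) above standard of care". The first use of the word risk in the limit is read here as the posterior probability, because the matching harm rule in 4.2.2.1 says probability.

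Section 9.1.1 defines a DLT as a CTCAE v5 event of Grade 3 or higher that is "independently assessed to be possibly or probably related to the IMP as per SRC charter". This is a deliberate choice: "The assessment of relatedness is included in the DLT definition for this CST", because severe events from the disease or co-morbidity may be frequent in these inpatients. The phase I primary endpoint in section 3.1 uses the same definition: "adverse events possibly or probably related to the IMP) up to day 8".

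On what controls receive, section 8.2.2 says: "Participants will be randomised to receive IV Favipiravir or SoC only (2:1) on Day 1". Section 4.2.1 makes phase I open-label. Section 6 names favipiravir and placebo as the investigational products, and section 6.1 restricts placebo to phase II. On cohort size, the synopsis says: "Each cohort includes 4 IV Favipiravir patients and 2 SoC".

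**The concern.** Relatedness to the IMP and subtraction of a concurrent control are two ways of taking out background toxicity. The protocol writes both into the dose rule and does not say how they combine. A patient who never receives the IMP has no stated route to an IMP-related event, so the quantity being subtracted is zero by construction.

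If the model treats it as zero, the comparative wording is only misleading. If the model carries an SoC parameter and lets it sit above zero, the rule removes background that the relatedness test has already removed, and the limit on toxicity truly attributed to the drug becomes looser than the figures suggest. This rule labels doses safe, and the model recommends the next dose and the phase II dose.

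**Working it through.** The protocol states no phase I operating characteristic, SoC event rate or prior, so there is no figure on this point to reproduce. The cohort totals are consistent: 5 × 6 = 30 and 7 × 6 = 42.

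**Inputs from the protocol**
- Safety limit: excess of 30%, probability cut-off 25% (10.3.1, repeated in 4.2.2.1).
- Target: excess of 20%, interval 15 to 25% (10.3.1).
- DLT: Grade 3 or higher and possibly or probably IMP-related (9.1.1, 3.1).
- IMPs: favipiravir and placebo (6); placebo in phase II only (6.1).
- Cohort: 4 active and 2 SoC (synopsis).

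**Step 1. SoC risk under the written definition.** Let p1 be the DLT risk on active and p0 the DLT risk on SoC. An SoC patient in phase I receives neither favipiravir nor placebo, so no event can be related to an IMP received. Hence p0 = 0.

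**Step 2. What the rule becomes.** On the absolute scale, a dose is safe if P(p1 − p0 ≥ 0.30) < 0.25. With p0 = 0 this is P(p1 ≥ 0.30) < 0.25, and the target is p1 = 0.20 (0.15 to 0.25). The rule can still be run, but as an active-arm rule. Read as a relative increase, it would have no content, since 1.3 × 0 = 0.

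**Step 3. What happens if SoC is given a non-zero DLT risk.** Values of p0 are assumed; the limit on p1 is p0 + 30% and the target is p0 + 20%.

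| Assumed p0 | Limit on related DLT risk | Target related DLT risk |
|---|---|---|
| 0% | 30% | 20% |
| 10% | 40% | 30% |
| 20% | 50% | 40% |
| 30% | 60% | 50% |
| 40% | 70% | 60% |

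Such shifts would be proper if events of any cause were counted in both arms, because p1 would then contain the same background. They are not proper here, because p1 counts only related events.

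**Step 4. Direction.** For any p0 ≥ 0, p1 − p0 ≥ 0.30 implies p1 ≥ 0.30. For the same posterior on p1, a non-zero p0 can therefore only lower the probability compared with 25%, so the rule becomes more lenient. A joint dose model could also change the posterior on p1, and these documents give no means of sizing that.

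**Step 5. SoC patients.** They number 5 × 2 = 10 of 30 as planned, or 7 × 2 = 14 of 42 at most. Under the written definition they add no DLT information to the formal rule.

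**The case against.** The strongest reply is that the deciding texts lie elsewhere. Section 4.2.1 refers dose-finding to the master protocol, 10.3.1 does the same for the modelling and analysis, and relatedness is judged under the SRC charter. None of these is at hand. An assessor masked to arm could rate an SoC event as possibly drug-related, and the comparison would then have content. This stands as a condition on the finding. It does not remove it: independent assessment is not the same as masked assessment, phase I is open-label, and nothing in this protocol says SoC events are rated that way. The conflict is between two sections of this document, one of them a definition specific to this candidate.

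The synopsis lists SoC beside favipiravir in its investigational-product row. Section 6 defines the IMPs expressly and leaves SoC out.

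It is also fair that the rule still works with SoC at zero, and that the target wording is additive, so the relative reading is strained. Both points stand.

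A reader might infer more: that the two treatments of SoC would give opposite verdicts after a first DLT. Simple sums seem to show it. With uniform priors and one DLT in 4 active patients against none in 2 SoC, the probability of an excess of at least 30 points is 0.21 if SoC is estimated (safe) and 0.53 if it is fixed at zero (unsafe). The documents do not support this inference. They give no priors, and a uniform prior on the active risk already places 1 − 0.30 = 0.70 above the limit before anyone is dosed, so it would reject the starting dose on no data. If the SoC prior is held near zero, as with Beta(0.1, 9.9) (mean 0.1/10 = 1%), the result after the same data differs from SoC fixed at zero by at most about 0.016. The apparent reversal comes mainly from the assumed priors.

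**Conclusion.** The dose limit and target in 10.3.1 are wrongly expressed as they stand. They are contrasts with an SoC DLT risk that the definition in 9.1.1 makes structurally zero. The conclusion rests on the text shown and on there being no masked rating of SoC events in the SRC charter.

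The size depends on the coded model. If SoC is fixed at zero, only the wording is affected. If SoC is given a DLT risk, each assumed percentage point loosens the limit and raises the target by one point, for example to 40% and 30% at an assumed 10%. No claim is made that any particular dose decision would reverse.

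Nor does it follow that the rule is unusable or the SoC patients wasted; they still serve the randomised safety, virological and clinical comparisons. Harm is limited because the SRC decides after reviewing all available safety data to Day 8 (4.2.1.1), and adverse events of any cause are also a phase I primary endpoint (3.1). The point is worth correcting, but it does not invalidate the design.

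**What to change.** In 10.3.1, restate the limit on the active arm: *a dose is deemed safe if the probability that the DLT risk on IV Favipiravir is 30% or more is less than 25%*. State the target as an active-arm DLT risk of 20% (15 to 25%), and delete the references to standard of care in both sentences. In 4.2.2.1, point the harm rule to the DLT definition in 9.1.1; it now gives the same 30% and 25% figures for CTCAE toxicity without citing that definition. Check that the coded model fixes the SoC DLT risk at zero.

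The cost is about three sentences and a model check, with no extra patients or data. If the model now has an SoC parameter, removing it makes the rule stricter, and the operating characteristics and the 25% cut-off need re-checking.

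If the SRC charter already has events in both arms rated masked to arm, say so in 9.1.1 and keep the comparison, worded as an absolute difference in percentage points. Counting all Grade 3 or higher events in both arms regardless of cause would also make the comparison meaningful, but it would undo the reasoned choice in 9.1.1, so it is a trade-off for the sponsor and not the preferred correction.

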##### Analyses

Please refer to the AGILE master protocol phase I analysis section 10.3.1. Bayesian credible intervals will be the 95% equal-tail intervals.

#### 10.3.2 Phase II

**Note this section differs from the AGILE Master Protocol.**

Once the recommended phase II dose, as defined by the safety and tolerability data in Phase I has been identified, Phase II will start. In the first stage 66 patients will be equally randomised between Favipiravir or placebo. If the probability of the treatment effect (in terms of the viral load on Day 3) for the experimental arm being below 0 (i.e., in favour of Favipiravir) is more than 0.94, the study will stop for efficacy; if this probability is less than 0.3, then the study will stop for futility. Within this range, the trial will be expanded to stage 2 where an additional 132 patients are equally randomised between Favipiravir and placebo. Safety will be reviewed by a DMEC at regular intervals.

##### Efficacy population

An evaluable patient for the study will be all patients randomised to Favipiravir or placebo (intention-to-treat).

## **Analysis**

Patients will be analysed according to the treatment to which they were randomised (efficacy population). In addition, a supplementary analysis of the primary endpoint will be conducted in all patients for whom there were no major protocol deviations that could impact treatment efficacy (to be defined in the statistical analysis plan).

The primary efficacy endpoint in phase II of the SARS-CoV-2 viral load (in log10) will be analysed using a Bayesian repeated measures model including all post-randomisation assessments up to and including Day 3. The model will adjust for treatment, baseline viral load, visit timepoint and interaction of treatment by visit, with a subject-specific random-effect and unstructured variance-covariance matrix. A non-informative (vague) prior will be used for all model parameters. Viral load data will be log10-transformed prior to analysis with treatment differences expressed on the log10 scale. If 94% of the posterior distribution of the treatment effect is below 0 (i.e. in favour of Favipiravir), the study will conclude the treatment is efficacious, at the interim or the final analysis.

For any deaths in the trial, the change in viral load will be assumed to be zero from the last measured timepoint. To assess the impact of missingness in the primary analysis due to missing data that are not missing at random (including death) sensitivity analyses will be performed. Details will be provided in the statistical analysis plan.

Once the last participant recruited completes the Day 29 assessment the data will be unblinded to allow a primary readout of this endpoint. Participants will continue to complete the remaining scheduled assessments and will not be unblinded at an individual level.

Further details on analysis methods for other endpoints will be detailed in a detailed SAP, which will be finalised and signed off prior to database lock.

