| Pharmacokinetic objective: To characterise the plasma PK of IV Favipiravir                                                                                                                                                                                                                                                                          | 
 
• PK parameters of IV Favipiravir up to Day 8
 
                                                                                                                                                                                                                                                                                                                                                                                                                                                                                                                                                                                                                                                                                                |
| Virological objective: To investigate the efficacy of IV Favipiravir on SARS-CoV-2 viral load                                                                                                                                                                                                                                                       | 
 
• Change from baseline over time, up to Day 29, in viral load
 
• Time to negative viral titres (Day 1-29)
 
                                                                                                                                                                                                                                                                                                                                                                                                                                                                                                                                                                                                                            |

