## 5.1 INCLUSION CRITERIA

The main trial (Phase I and II) inclusion criteria are outlined in the AGILE Master Protocol and listed below.

1. Adult in-patients ( $\geq 18$  years) with laboratory confirmed COVID-19 infection by positive polymerase chain reaction (PCR) test within 7 days of randomisation
2. Ability to provide informed consent signed by study patient or legally acceptable representative
3. Women of childbearing potential (WOCBP) and male patients who are sexually active with WOCBP must agree to use a highly effective method of contraception (as outlined in section 5.4 below) from the first administration of trial treatment, throughout trial treatment and for the duration outlined in the candidate-specific trial protocol as well as addition 14 days for women and 7 days for men after the last dose of trial treatment.

Additional criteria specific to this candidate are:

4. Group A and B (moderate to severe disease). Patients with clinical status of Grades 4 (hospitalised, no oxygen therapy), 5 (hospitalised, oxygen by mask or nasal prongs), 6 (hospitalised, on non-invasive ventilation, or high flow oxygen) as defined by the WHO Clinical Progression Scale (WHO, 2020).
5. Less than or equal to 14 days from onset of COVID-19 symptoms

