#### Phase II

Participants will be randomised to receive IV Favipiravir or saline placebo (alongside SoC) on Day 1. Refer to section 6 of the CST6 protocol for further information.

**8.2.3 Daily Day 2 through to Day 14:** when in hospital or via telephone contact if leaves hospital before day 8 to document: adverse events and concomitant medication. First 5 days of treatment, daily SARS-CoV-2 surveillance NP swab. The following as per SoC and if clinically indicated if in hospital:

- Full blood count, U&Es, Uric acid, estimated GFR, LFTs
- Vital signs
- Assessment of oxygen use
- Targeted physical exam

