### 8.2.4 Specific Assessments on Days 3, 5, 8 and 11 ( $\pm 1$ day)

The following assessments are to be carried out on 3, 5, 8 and 11 (NB day of randomisation and start date of treatment is Day 1).

- SARS-CoV-2 surveillance NP swab
- Full blood count
- Urea and electrolytes

- Estimated GFR
- Liver Function Tests
- Uric acid
- Concomitant medication and standard of care review
- AE assessment
- Translational swab (Days 3 and 5 only)

In addition, for CST6 candidate specific trial protocol the following are required:

- Assessment using the WHO Clinical Progression Scale (WHO, 2020):
  0. Uninfected, no viral RNA detected
  1. Ambulatory mild disease, asymptomatic; viral RNA detected
  2. Ambulatory mild disease, symptomatic; independent
  3. Ambulatory mild disease, symptomatic; assistance needed
  4. Hospitalised moderate disease, no oxygen therapy (If hospitalised for isolation only, record stats as for ambulatory patient)
  5. Hospitalised moderate disease, oxygen by mask or nasal prongs
  6. Hospitalised severe disease, oxygen by NIV or high flow
  7. Hospitalised severe disease, intubation and mechanical ventilation  $pO_2/FiO_2 \geq 150$  or  $SpO_2/FiO_2 \geq 200$
  8. Hospitalised severe disease, mechanical ventilation  $pO_2/FiO_2 < 150$  ( $SpO_2/FiO_2 < 200$ ) or vasopressors
  9. Hospitalised severe disease, mechanical ventilation  $pO_2/FiO_2 < 150$  and vasopressors, dialysis, or ECMO
  10. Dead
- Non-Ventilated Patients: National Early Warning Score 2 (NEWS2) Assessment:
  - Respiration rate
  - Oxygen saturation
  - Systolic blood pressure
  - Pulse rate
  - Level of consciousness or new confusion\*
  - Temperature

\*The patient has new-onset confusion, disorientation and/or agitation, where previously their mental state was normal – this may be subtle. The patient may respond to questions coherently, but there is some confusion, disorientation and/or agitation. This would score 3 or 4 on the GCS (rather than the normal 5 for verbal response), and scores 3 on the NEWS system.
- Assessment of oxygen use (low flow, high flow, mechanical flow, mechanical ventilation use) (only if supplemental oxygen is not administered) – daily whilst in hospital
- Targeted Physical examination
- Blood (plasma and DBS) taken for PK assessments on Day 3 (pre-dose, 0-1 hr, 2-4 hr, 6-12 hr post completion of first infusion) and Day 5 (0-1hr, 6-12 hr post completion of first infusion)

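### The primary Phase II model puts a subject random effect on top of an unstructured covariance matrix, leaving one redundant variance parameter that vague priors cannot settle

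*Protocol*

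**What the plan says.** The Analysis paragraph of protocol section 10.3.2 defines the primary efficacy model. It is a Bayesian repeated measures model of log10 viral load "including all post-randomisation assessments up to and including Day 3". On the mean structure: "The model will adjust for treatment, baseline viral load, visit timepoint and interaction of treatment by visit". On the covariance, the model is fitted "with a subject-specific random-effect and unstructured variance-covariance matrix". On priors: "A non-informative (vague) prior will be used for all model parameters".

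The trial acts on one output of this model, the posterior probability that the Day 3 effect favours favipiravir. Above 0.94 it stops or concludes for efficacy, at the interim or the final analysis. Below 0.30 at the interim it stops for futility (sections 4.2.2 and 10.3.2).

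Section 10.3.2 defers to the SAP the definition of major deviations, the missing-data sensitivity analyses and the methods for other endpoints. It does not defer the primary model, so the specification is the protocol's own.

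On the data available: "First 5 days of treatment, daily SARS-CoV-2 surveillance NP swab" (section 8.2.3). Eligibility allows "Less than or equal to 14 days from onset of COVID-19 symptoms" (section 5.1). Symptom onset and WHO grade are recorded at screening (section 8.1), and WHO grade again at baseline (section 8.2.1).

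**The concern.** An unstructured matrix already gives every visit its own variance and every pair of visits its own covariance. A subject random intercept adds the same constant to all of those entries, so the matrix can absorb it completely. The data cannot separate the two, and vague priors supply nothing that would.

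The go/no-go rule is a threshold on a simulated posterior probability. If the sampler moves slowly along a direction the likelihood does not constrain, two competent analysts running the same specification could report different probabilities near 0.94 or 0.30. Under one common meaning of non-informative, the posterior as specified does not exist as a proper distribution.

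Separately, patients may enter anywhere up to 14 days from symptom onset and in three WHO grades, and the model adjusts for neither.

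**Working it through.** **1. The plan's own figures.** Inputs: 33 per arm at the interim and 99 per arm at the end (66 and 198 patients, 1:1), SD 1.5, thresholds 0.94 and 0.30 (sections 10.2 and 10.3.2). With a vague prior the posterior probability is Φ(Z), so the limits on Z are 1.555 for efficacy and −0.524 for futility. Information is n/(2 × 1.5²): 33/4.5 = 7.33 and 99/4.5 = 22.0. The mean of Z is the effect times the square root of the information; for 0.5 log10 at the interim it is 0.5 × √7.33 = 1.354. Integrating over both looks:

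| True effect (log10) | Efficacy at interim | Futility at interim | Efficacy overall |
|---|---|---|---|
| 0 | 0.060 | 0.300 | 0.0998 |
| 0.5 | 0.420 | 0.030 | 0.804 |
| 0.6 | 0.528 | 0.016 | 0.904 |

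The stated 80%, over 90% and below 10% all reproduce. The variance split does not enter this calculation.

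**2. Parameter count.** Day 1 is the baseline covariate and swabs are daily, so I take the modelled visits to be Days 2 and 3; the protocol does not say so. Write the marginal covariance as V = R + s²J, with R unstructured, s² the random-intercept variance and J a matrix of ones. Two visits give 3 estimable entries in V, against 3 + 1 = 4 parameters; the map has rank 3. Four visits would give 10 entries against 11 parameters. The excess is always one.

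**3. What stays identified.** (R, s²) and (R + cJ, s² − c) give the same V, hence the same likelihood. The Day 3 contrast depends on V alone. One simulated dataset per sample size (SD 1.5, assumed visit correlation 0.7), using a sampler that integrates out the random effect when drawing the treatment effect, under four prior or starting settings:

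| Per arm | Unstructured only: mean (SD) | With random effect: means (SDs) |
|---|---|---|
| 33 | −1.005 (0.333) | −1.000 to −1.006 (0.343–0.345) |
| 99 | −0.161 (0.227) | −0.159 to −0.162 (0.225–0.230) |

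**4. The split follows the prior.** In the same 33-per-arm dataset the 95% interval for s² was 1.10–2.24 under one vague prior setting and 0.23–2.08 under another.

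**5. Impropriety.** Hold V fixed. The determinant of R = V − s²J is |V|(1 − k s²), with k = 1′V⁻¹1. The standard non-informative prior for a 2 × 2 covariance is |R|^(−3/2). The likelihood is flat in s², so the posterior needs the integral of (1 − k s²)^(−3/2) from 0 to 1/k. Stopping a fraction e short of the limit gives (2/k)(e^(−1/2) − 1). For e = 0.1, 0.01, 0.0001 and 0.000001 the bracket is 2.16, 9, 99 and 999. It diverges. A further prior on s² that is positive at that limit does not cure this.

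**6. Sampler risk.** A naive sampler that draws fixed and random effects in turn gave effective sample sizes of 7–65 from 4,500 draws for the treatment effect; with the unstructured matrix alone it was 4,500. As a rough guide, the Monte Carlo error of a probability near 0.94 is then √(0.94 × 0.06/65) = 0.03 to √(0.94 × 0.06/7) = 0.09. Over many trials, noise at an effective size of 65 moves type I error only to about 10.2%. The damage is to the reproducibility of a single borderline decision.

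**7. Covariates.** Take 1.5 as the residual SD and let symptom duration and WHO grade explain a share R² of the remaining variance (an assumption), so information is divided by 1 − R². Power at 0.5 log10 goes from 0.804 to 0.820 at R² = 5% and 0.836 at 10%.

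**The case against.** The best defence is that this is wording. The sentence says neither intercept nor residual, and it can be read as a single unstructured matrix describing within-patient dependence. No endpoint or decision rule uses the variance split, and a well-built sampler with proper priors gives almost the same answer either way. Most of this stands, and it is why the point is limited to the specification. It does not remove the point: the text names two components, the primary model is not deferred to the SAP, and the literal form is improper under a standard choice of prior.

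On covariates, the defence is that adjusting for baseline viral load alone contradicts nothing, and that section 10.1 names no stratification factor. That stands too. The 5–10% is not in the documents, and section 10.2 gives 1.5 as the SD of change from baseline, not the residual after baseline adjustment. The addition is an improvement, not a correction.

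A reader might infer three stronger things that the documents do not support.

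- **That the model as a whole is not identifiable.** Step 3 shows that only the split is.
- **That the Day 4 and 5 swabs are wasted and would sharpen the Day 3 contrast.** They serve a secondary endpoint, "Change from baseline over time, up to Day 29, in viral load". With treatment-by-visit means and an unstructured covariance they add nothing when Day 3 is observed. Under assumed intermittent missingness of 5–30% they cut its standard error by only 0.3–4.2%, and by nothing if patients who miss Day 3 also miss Days 4 and 5.
- **That a Day 3 visit held on Day 4, within the ±1 day window of section 8.2.4, is lost.** The model works by visit timepoint, so such a swab can count as Day 3. Mapping windows to visits is ordinary SAP content, and the SAP is not at hand.

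**Conclusion.** The point holds for the covariance specification. Read literally, section 10.3.2 sets up a model with one redundant variance parameter. Its split is decided by the prior alone, and its joint posterior is improper under the standard non-informative covariance prior. The practical risk is poor convergence of the one probability compared with 0.94 and 0.30. There is no general bias, and the stated operating characteristics are not in doubt (type I error 0.0998, power 0.804 and 0.904).

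This rests on reading the text as a random intercept plus a residual matrix. The count of 4 against 3 also rests on Days 2 and 3 being the modelled visits, but the redundancy does not. The sampler figures come from simulated data and show what can happen, not what will. The covariate gain of about 1.6 to 3.2 percentage points of power depends entirely on the assumed 5–10%.

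**What to change.** Amend the model sentence in section 10.3.2, and carry it into the SAP, before the interim analysis:

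- Delete the subject random effect and keep an unstructured within-patient covariance across the post-baseline visits. If that was always the meaning, say that the unstructured matrix is the marginal one.
- Replace the blanket vague-prior statement, for the covariance, with proper weakly informative priors named in advance.
- Optionally, add days from symptom onset and baseline WHO grade as fixed effects.

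The cost is a one-sentence amendment and slightly more programming. No extra data are collected and neither the sample size nor the thresholds change. The treatment contrast is the same quantity under the simpler covariance.
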